### Participant timeline

The timeline for participants in the study is shown in Figs. 1 and 2. Adult patients referred to an infectious disease physician or orthopaedic surgeon for the treatment of orthopaedic infection, whose treatment plan includes surgical management and local antibiotic therapy, will be considered for inclusion in the study.

**Fig. 1 Fig1:**
[figure not shown]
*Flow diagram* of participant enrolment, randomisation, treatment and follow-up within the SOLARIO study

**Fig. 2 Fig2:**
[figure not shown]
SPIRIT Schedule of enrolment, interventions and assessments in the SOLARIO study

Local clinical research staff will seek informed consent to participate in the study from eligible patients. After receipt of the Patient Information Sheet, potential participants will be encouraged to discuss the study with the clinical care team and/or personal contacts and to ask questions. The Patient Information Sheet and Informed Consent Form state clearly that taking part in the study is voluntary and that refusal or withdrawal carry no detriment to usual clinical care. Patients not felt to have capacity to consent to study participation will not be approached and proxy consent will not be allowed. This trial does not involve any study-specific outpatient appointments, investigations or hospital visits. Hence, there will be no expenses or other payments to participants in this study.

Potential participants will be afforded up to seven days after their surgery to decide whether they wish to take part. Those that provide fully informed consent will be randomised through a centralised electronic database with stratification by study site only.

Participants will be followed up during routine care visits at the local centre. The frequency and timings of routine care visits will vary depending on the clinical condition and management pathways of individual patients. Trial-specific data collection points will be at: (1) 6 weeks (± 1 week); (2) once between 3 and 6 months; and (3) 1 year (± 1 month) after randomisation. There will be no trial-specific clinic visits. Either the patient or the patient’s GP will be asked for follow-up data if information relating to outcome measures is not available through routine care visits at these times.

### Sample size

A total of 500 participants will be recruited into this study (250 in each arm). This is based on an anticipated failure rate of up to 13% in the study population overall, 90% power to demonstrate non-inferiority with a non-inferiority margin of 10%. Corresponding simulations indicated a necessary total sample size of 492, rounded up to 500. Deviation from protocol will be accounted for through per-protocol and intention-to-treat analyses conducted in parallel for outcomes relating to infection recurrence.

### Strategies for ensuring adequate enrolment for sample size

Recruitment at the proposed centres, which were identified from a previous study of treatment strategy for orthopaedic infection as high recruiting centres that also extensively used local antibiotic therapy [3], will help 500 participants to be enrolled into the trial during a 24-month recruitment period. Additional centres will also be approached to improve recruitment.

### Assignment of interventions and allocation concealment

Participants will be allocated to short or long systemic antibiotic treatment at random in a 1:1 ratio within seven days after index surgery.

Randomisation using permuted blocks, stratified by treatment centre only, is allocated through the Clinical Database Management System (CDMS). Research enrolment and randomisation will be performed by the local clinical research staff for participants who give informed consent to participate in the study. Allocation concealment is inherent to the software used for randomisation.

Back-up offline randomisation will be available and is described in Additional file 1.

The generation of randomisation sequences is described in Additional file 1.

### Blinding

This is an open-label study; only the blinded Endpoint Committee will be unaware of the participant’s treatment allocation when assessing potential primary endpoints using redacted patient records. Information that may inadvertently disclose treatment allocation will be redacted, including antibiotic use, antibiotic side effects, antibiotic monitoring and means of antibiotic administration (including venous catheterisation).

### Data collection and management

Data will be collected through an electronic case report form within a CDMS. Validation, additional data entry instructions and scheduling will be employed within the CDMS to improve data quality and assist contemporaneous recording. Data will be stored securely and will be accessible by non-clinical research staff for authorised data monitoring purposes only. Data entry and database access will be fully logged and audited. Missing data will be sought by local study clinicians by telephone from participants or their GP if consent for this has been provided. Anonymised data without patient identifiable information will be used for analysis.

Participants whose treatment deviates from allocated treatment strategy will be followed up within the study in the same way to enable analysis by intention to treat.

### Statistical analysis

The non-inferiority margin is 10%, i.e. a tolerance of < 10 additional treatment failures for every 100 patients treated. This margin has been used in previous studies of bone infection [40]. Nine out of 16 patient representatives at the Nuffield Orthopaedic Centre, Oxford, UK, with experience of orthopaedic illness, voluntarily involved in the design of this study, preferred to accept an 8/10 chance of cure for orthopaedic infection rather than endure four weeks of emphasised severe side effects for a 9/10 chance of cure. However, 4/16 patient representatives would not accept a decrease in the chance of cure from 99% to 98% to avoid four weeks of severe antibiotic side effects, highlighting the individual nature of this decision.

For the purpose of the primary analysis, participants experiencing definite treatment failure by 12 months (as classified by the blinded Endpoint Committee) will be regarded as treatment failures and all other patients as free from treatment failure. Though the absolute rate of treatment failure may not be accurately estimated this way, the size of the risk difference between the two treatment arms is an appropriate estimate of the true difference. A formal assessment of the difference between the two arms will be based on the risk difference with a 95% confidence interval and a one-sided test (*p* = 0.025) to reject the null hypothesis that the risk difference is greater than the non-inferiority margin. Both intention-to-treat and per-protocol comparisons of the failure rate between the two treatment arms will be included as part of the primary analysis and non-inferiority will be required in both analyses to support the conclusion of short systemic antibiotic treatment non-inferiority in this study.

Further contingency analyses will compare the proportion of additional possible and probable treatment failures in both treatment arms.

Comparison of proportions of participants experiencing the primary endpoint, rather than time-to-event analysis, has been chosen because participants experiencing symptoms of infection recurrence would be very likely to seek review at their specialist centre or have information pertaining to specialist review available through their GP; the assumption of non-informative censoring would not be met.

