### Outcomes

Endpoints will be identified by prospective surveillance throughout the year after randomisation. This study is an open-label trial, but the ascertainment of outcomes will be carried out by an endpoint committee who will be blind to the participant’s treatment allocation (blinded Endpoint Committee).

The definitions of infection recurrence used in this study are based on internationally accepted standards [9, 10, 38] with minor modifications. They have been applied in a previous study in orthopaedic infection [3].

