### Primary endpoint

The primary endpoint will be definite treatment failure within 12 months of surgery, as determined by a blinded Endpoint Committee using notes from the patient records redacted for names of patients and clinicians, as well as information that might betray the allocated treatment strategy. The criteria for definite, possible and probable treatment failure are available in the Additional file 1.

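### Counting everyone without a classified definite failure as failure-free does not leave the risk difference intact: failures missed equally in both arms shrink it and make non-inferiority easier to declare

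*Protocol article*

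**What the plan says.** Under Statistical analysis, the rule for participants whom the blinded Endpoint Committee judges to have failed definitely by 12 months is that they "will be regarded as treatment failures and all other patients as free from treatment failure". No separate category exists for people who withdrew, were lost or were last seen early, so they fall among the failure-free. The next sentence accepts that the absolute failure rate may be inaccurate as a result, but maintains that "the size of the risk difference between the two treatment arms is an appropriate estimate of the true difference".

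The formal comparison is the risk difference "with a 95% confidence interval and a one-sided test" at the 0.025 level, "to reject the null hypothesis that the risk difference is greater than the non-inferiority margin". The margin is 10 percentage points. Intention-to-treat and per-protocol comparisons both belong to the primary analysis, and both must show non-inferiority.

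On follow-up, the Outcomes section says "Endpoints will be identified by prospective surveillance throughout the year after randomisation". The Participant timeline section says "There will be no trial-specific clinic visits". Data come from routine care, with the patient or GP asked when information is missing. The last collection point is 1 year ± 1 month after randomisation, whereas the Primary endpoint section defines the outcome as "definite treatment failure within 12 months of surgery".

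The Statistical analysis section also argues that patients with recurrent symptoms would very probably return to their specialist centre or be traceable through their GP. No expected rate of loss or of missed failures is given.

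**The concern.** The article treats incomplete ascertainment as something that distorts the two rates but cancels in their difference. Proportional under-counting does not cancel in a difference. It cancels in a ratio. When the same share of failures goes unseen in each arm, the arm with more failures loses more of them, and the gap narrows.

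In a superiority trial that would cost power. Here it moves the estimate away from the 10-point margin towards zero when the short course is truly worse, which is the situation the test has to guard against. The one-sided 2.5% error rate is then not held, and less complete follow-up makes the trial easier to win. The rule is also the stated primary analysis, so the error sits in the main conclusion.

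**Working it through.** **Inputs from the protocol article.** 250 per arm; anticipated failure rate up to 13% overall; margin 10 points; one-sided 0.025; 90% power; stated total 492, rounded up to 500 (Sample size and Statistical analysis).

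**Assumed inputs.** True rates exactly at the margin: 23% short and 13% long, with 18% and 8% as a second case. The share m of true failures that are missed is not given, so it is varied from 0 to 20%.

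**Step 1: the plan's own figure.** With 13% in each arm, the unpooled normal formula gives 238 per arm (476 in total). The Farrington–Manning score formula gives 248 per arm (496), within 1% of 492. Exact power at 246 per arm is 90.3% (score test) or 91.0% (Wald). The sample size reproduces, so the planning inputs are read correctly.

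**Step 2: what the counting rule does.** If a share m of failures is missed and counted as failure-free, a true rate p is observed as p(1 − m). With equal m in both arms:

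observed difference = p_S(1 − m) − p_L(1 − m) = (1 − m)(p_S − p_L)

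The ratio p_S/p_L is unchanged and the difference is not. At m = 10% the rates are 0.23 × 0.90 = 20.7% and 0.13 × 0.90 = 11.7%, a difference of 9.0 points instead of 10.

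**Step 3: effect on the error rate.** Exact binomial enumeration at 250 per arm, declaring non-inferiority when the upper Wald 95% limit is below 10 points:

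| Share of failures missed, both arms | Observed difference (points) | False non-inferiority, 23% v 13% | False non-inferiority, 18% v 8% |
|---|---|---|---|
| 0% | 10.0 | 2.6% | 2.8% |
| 2.5% | 9.75 | 3.1% | 3.3% |
| 5% | 9.5 | 3.7% | 4.0% |
| 10% | 9.0 | 5.2% | 5.9% |
| 15% | 8.5 | 7.2% | 8.5% |
| 20% | 8.0 | 9.9% | 12.0% |

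The score test gives slightly lower figures with the same pattern (23% v 13%: 2.5% at m = 0, 4.8% at 10%, 9.1% at 20%).

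**Step 4: unequal missing (23% v 13%).**
- 15% missed short, 5% long: 0.23 × 0.85 − 0.13 × 0.95 = 0.1955 − 0.1235 = 7.2 points; error 14%.
- 5% missed short, 15% long: 0.23 × 0.95 − 0.13 × 0.85 = 0.2185 − 0.1105 = 10.8 points; error 1.5%.

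**Step 5: when the claim is right.** The observed difference equals the true one if no failures are missed, if the true difference is zero and missing is equal, or if the arm-specific losses happen to cancel.

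**Step 6: the time window.** Randomisation is within seven days of surgery, and the last collection point may fall 1 month before the first anniversary of randomisation. It can therefore close up to about one month before 12 months after surgery, and the rule counts any unobserved remainder as failure-free.

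**The case against.** The strongest reply is that few failures will be missed. The article describes surveillance through the year, event-triggered reporting to the Endpoint Committee, and patient, GP or telephone contact where data are missing. It also expects people with recurrence to come back or be traceable. As an assumed illustration, suppose 10% of participants are lost evenly over the year at constant hazard, and half of their later failures are traced. Then m is about 10% × ½ × ½ = 2.5%, and the error is 3.1% to 3.3%. This stands as an argument about size. It does not make the article's general statement true.

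Several stronger readings are tempting but not supported:

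- A reader might take the percentages in the table as loss to follow-up. They are shares of failures missed. The two coincide only if everyone lost is lost at the start and none of their failures is ever traced.
- A reader might infer that the bias always favours the short course. With unequal missing it can run either way, and nothing in the article says which arm would be followed less completely.
- A reader might infer that requiring both analysis sets gives no protection. If the per-protocol set uses the same counting rule on the same people, it gives none. But this article does not define that set. If it requires 12-month follow-up, lost participants would drop out of it.
- The early edge of the last collection window is a minor contributor: about a month at most, with surveillance said to run throughout.

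It is also fair that simple imputation has its own weakness. The article itself says non-informative censoring would not hold. If failures are preferentially seen, imputation that assumes missing outcomes resemble observed ones would overstate failure rates. Sensitivity analyses may exist in Additional file 1 or an analysis plan, neither of which is shown. They would not change the stated primary rule or its justification.

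**Conclusion.** The point holds. The counting rule and the sentence defending it are stated in the article, and the sentence is wrong as a general claim. Under equal missing, the rule multiplies the risk difference by (1 − m) and is anti-conservative for non-inferiority.

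The size depends on a quantity the article does not give. With 23% v 13%, 250 per arm and a Wald limit, the nominal 2.5% error becomes roughly 3% to 4% if 2.5% to 5% of failures are missed, about 5% at 10%, and about 10% at 20%. If tracing works as the article expects, the lower end applies. The figures are for a single analysis; a false conclusion on both required analyses can be no more frequent. They show what the rule would do, and do not predict that the trial's error rate will be 5% or more.

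**What to change.** 1. Delete the statement that the risk difference is unaffected.
2. Count a participant as failure-free only when status through 12 months after surgery is confirmed from clinic, patient or GP records.
3. Align the last data collection point so that it does not close before 12 months after surgery.
4. Treat unconfirmed outcomes as missing in the primary risk difference, for example by multiple imputation using site and status at earlier data points.
5. Report alongside it the result under the current rule, and a prespecified sensitivity analysis in which short-arm participants with missing outcomes have higher failure rates. These inform interpretation. The conclusion should not be made conditional on surviving the sensitivity analysis, because the right assumption about missing outcomes is a matter of judgement here.

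The cost is wording, some analysis, a somewhat wider interval and lower power. At 13% in both arms, Wald power is about 91.5% with 250 informative participants per arm, 88.2% with 225 and 84.6% with 200. The planned 500 against a computed 492 leaves almost no allowance, so complete tracing of 12-month status matters more than the choice of imputation model. No trial-specific visits are needed.

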**Methods:**

SOLARIO is a multicentre open-label randomised controlled non-inferiority trial comparing short and long systemic antibiotic therapy alongside local antibiotic therapy. Adult patients with orthopaedic infection, who have given informed consent, will be eligible to participate in the study provided that no micro-organisms identified from deep tissue samples are resistant to locally implanted antibiotics. Participants will be randomised in a 1:1 ratio to receive either a short course (≤ 7 days) or currently recommended long course (≥ 4 weeks) of systemic antibiotics. The primary outcome will be treatment failure by 12 months after surgery, as ascertained by an independent Endpoint Committee blinded to treatment allocation. An absolute non-inferiority margin of 10% will be used for both per-protocol and intention-to-treat populations. Secondary outcomes will include probable and definite treatment failure, serious adverse events, treatment side effects, quality of life scores and cost analysis.

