#### Secondary objectives

Secondary objectives of the present study are to compare the following secondary endpoints according to treatment allocation:
probable treatment failure and possible treatment failure;serious adverse events (SAEs), including death (i.e. all-cause mortality);antibiotic side effects related to the treatment of orthopaedic infection;resource allocation using (a) length of inpatient hospital stay, (b) frequency of outpatient visits, (c) antibiotic prescribing costs. In-hospital treatment cost analysis;quality of life as evaluated by the patient-reported outcome measures on the EQ-5D-5 L questionnaire at baseline and one-year follow-up;deviation from allocated treatment strategy, including additional antibiotic prescribing, and early termination of systemic antibiotics because of AEs, patient preference or any other reason.

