### Secondary endpoints

Secondary endpoints include probable and possible treatment failure, as determined by the blinded Endpoint Committee. Definitions and information about validation for these endpoint measures are available in the Additional file 1. Additional secondary endpoints, discussed below, will be determined by the research team at individual sites.

Symptoms potentially attributable to side effects of antibiotic treatment will be recorded on a three-point scale (absent, mild, severe) for all participants, regardless of whether antibiotics are taken at the time [39]. Five potential side effects, identified as having the highest impact by a group of 16 patient representatives, will contribute to a bivariate analysis; all additional reported symptoms that may represent antibiotic-related side effects will be similarly recorded on the three-point scale and reported as proportions of participants affected.

Quality of life will be assessed using the EQ-5D-5 L questionnaire administered at study enrolment and 12 months after surgical treatment of infection. For the enrolment questionnaire, patients will be asked to describe their health state immediately before index surgery. The mean difference between quality of life scores at baseline and 12 months will be compared. Permission to use the EQ-5D-5 L questionnaire was granted by the EuroQol Research Foundation.

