#### Bivariate analysis

The potential advantage of short systemic antibiotics (fewer side effects) versus the potential disadvantage (higher treatment failure rate) will be summarised at the patient level in an advantage score.

The advantage score is defined as the sum of predefined side effect scores at the first two follow-up timepoints: a 1-point increase is equivalent to, in either follow-up period, one level higher for one of each of the five predefined side effects or the presence of either *Clostridium difficile* diarrhoea or intravenous catheter-associated complication. A formal assessment of the difference between the two arms with respect to the advantage score will be based on the difference in mean values with a 95% confidence interval and a *p* value for the test of the null hypothesis of no difference between the treatment groups.

In addition, the difference in mean advantage score and the difference in treatment failure rate will be plotted in a two-dimensional plane together with a 95% confidence region. Furthermore, the ration between the scores will be reported together with a 95% confidence interval. This will allow assessment of the improvement in mean advantage score required for one more treatment failure in 100 patients in order to regard short systemic antibiotic treatment as beneficial. Further secondary analyses are described in Additional file 1.

Data monitoring, interim analysis and criteria for early discontinuation of the study are described in Additional file 1.

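### The supportive analysis of probable and possible failure is worded as an incremental comparison; prespecified cumulative risk differences would show whether the result holds under a broader failure definition

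*Protocol article*

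**What the plan says.** The protocol article sets out the infection outcomes in several places.

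- Primary endpoint: "The primary endpoint will be definite treatment failure within 12 months of surgery".
- Statistical analysis, on the primary analysis: participants with definite failure "will be regarded as treatment failures and all other patients as free from treatment failure". Probable and possible failures therefore count as successes.
- Statistical analysis, on the supportive analysis: "Further contingency analyses will compare the proportion of additional possible and probable treatment failures in both treatment arms".
- Secondary objectives list "probable treatment failure and possible treatment failure", and the Secondary endpoints section says: "Secondary endpoints include probable and possible treatment failure, as determined by the blinded Endpoint Committee". Neither says whether a definite failure also counts towards these endpoints.
- The abstract differs: "Secondary outcomes will include probable and definite treatment failure".
- Two matters are left to a supplement: "The criteria for definite, possible and probable treatment failure are available in the Additional file 1", and "Further secondary analyses are described in Additional file 1".

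The article nowhere states a nested comparison such as definite or probable failure.

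**The concern.** If the three categories are mutually exclusive, a participant adjudicated as a definite failure cannot also be an additional probable or possible one. The supportive numerator is then what remains after removing an outcome that may itself depend on treatment. An arm with more definite failures can look better on the remainder simply because its failures have already been counted.

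This matters because the Statistical analysis section concedes that counting only definite failures may misstate the absolute failure rate, while maintaining that the difference between arms is still appropriately estimated. The direct way to examine that statement is to estimate the same risk difference under a wider definition of failure. The incremental comparison, taken alone, does not do this.

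**Working it through.** **The plan's own figure.** The Sample size section gives 492 in total (rounded to 500) for a failure rate of up to 13%, a 10-point margin and 90% power, with one-sided 0.025 from the Statistical analysis section. A restricted-variance score formula gives 496, and enumeration with a score test gives 488. Power at 492 is 90.3% (score) to 91.0% (Wald). The figure reproduces, and the point here does not depend on it.

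**Inputs.** 250 per arm, from the Sample size section. The article gives no rates for probable or possible failure, so every count below is an assumption. Categories are taken as mutually exclusive, and differences are short minus long.

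**Formulas.** With exclusive categories, for each arm: total = definite + additional. Hence

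RD(total) = RD(definite) + RD(additional).

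Wald 95% CI: RD ± 1.96 × √[p₁(1−p₁)/250 + p₂(1−p₂)/250].

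**Worked case.** Additional 5 v 15: p₁ = 0.02, p₂ = 0.06, RD = -0.04. SE = √[(0.0196 + 0.0564)/250] = 0.0174, and 1.96 × SE = 0.034, so the interval is -7.4 to -0.6 points. Definite 35 v 25 gives +4.0, and 4.0 − 4.0 = 0.0 for the total.

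**Results (points, 95% CI).**

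| Case | Definite | Additional | Total |
|---|---|---|---|
| A | 35 v 25: 4.0 (-1.7 to 9.7) | 5 v 15: -4.0 (-7.4 to -0.6) | 40 v 40: 0.0 (-6.4 to 6.4) |
| B | 40 v 22: 7.2 (1.5 to 12.9) | 15 v 15: 0.0 (-4.2 to 4.2) | 55 v 37: 7.2 (0.4 to 14.0) |
| C | 45 v 20: 10.0 (4.2 to 15.8) | 8 v 20: -4.8 (-8.8 to -0.8) | 53 v 40: 5.2 (-1.6 to 12.0) |
| D | 34 v 26: 3.2 (-2.5 to 8.9) | 15 v 7: 3.2 (-0.4 to 6.8) | 49 v 33: 6.4 (-0.1 to 12.9) |
| E | 32 v 32: 0.0 (-5.9 to 5.9) | 28 v 10: 7.2 (2.6 to 11.8) | 60 v 42: 7.2 (0.2 to 14.2) |

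In A the additional comparison favours the short course although total failure is equal. In B it is null although total failure is higher on the short course. In C it has the opposite sign to the total. In D the two separate comparisons each have an upper limit below 10 while the total does not. In E the incremental comparison shows the whole difference, so it does not always mislead.

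Point estimates add across the two comparisons, but interval limits do not: in D, 8.9 + 6.8 = 15.7, whereas the correct upper limit from the summed counts is 12.9. The total's interval has to be computed from counts.

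**Margin on a wider endpoint.** By normal approximation with 250 per arm and equal true rates, power against 10 points is Φ(0.10/√[2p(1−p)/250] − 1.96). At p = 0.13 this is Φ(1.36), about 91%. At an assumed p = 0.20 it is Φ(0.84), about 80%. A wider endpoint can cross 10 points through lower precision alone.

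**The case against.** The other side has good points, and most of them stand.

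- *The plan may not be incremental.* The sentence could mean that these failures are added to the definite ones, and the supplement, which was not available for this check, may specify cumulative analyses. A reader might infer that the plan rules out a cumulative analysis. The article does not say so. What remains is that its one stated supportive analysis most naturally reads as incremental, and at best supports two different comparisons.
- *Nothing is hidden.* The definite-failure difference is the headline result and is read beside the supportive one. In cases B and C the primary upper limits (12.9 and 15.8) already exceed the margin. This stands: a reader might infer that a harmful difference would be concealed, but that requires ignoring the primary analysis.
- *The total can be recovered.* Once category counts are published, the cumulative difference and its interval follow directly. This also stands. It shows that no information is lost, but a later calculation is not a prespecified estimate, which matters more in an open-label trial.
- *The 10-point margin was not set for this endpoint.* The article supports it by its use in earlier bone-infection studies and by patients' views on chance of cure, and powers the trial for up to 13% failure. A formal non-inferiority test on an endpoint that includes possible failures is therefore not supported by the document.
- *The counts are invented.* True. They show what can happen, not how likely it is.

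**Conclusion.** The point holds as a limited one. Read naturally, the supportive comparison removes definite failures from its numerator, so by itself it does not test whether the risk difference survives a broader definition of failure. It can be null (case B) or opposite in sign (case C) relative to total failure. The article prespecifies no cumulative estimate.

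The conclusion rests on the incremental reading and on mutually exclusive categories; the size of the effect in this trial is unknown. A reader might go further and infer that the non-inferiority conclusion is undermined. It is not: that conclusion depends on definite failure in both the intention-to-treat and per-protocol analyses, and neither it nor the sample size changes. Nor does the document call this analysis its main robustness check. Severity is minor to moderate, as a free improvement.

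**What to change.** In the Statistical analysis section, replace the sentence with two nested cumulative endpoints: (1) definite or probable failure; (2) definite, probable or possible failure. Report each as a risk difference with 95% CI in the intention-to-treat and per-protocol sets, labelled supportive. The Sample size section already commits to both sets for recurrence outcomes. Keep the separate category counts by arm as description. The 10-point line may be drawn for reference, without a formal test.

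State in the Secondary endpoints section whether the categories are exclusive or nested, and reconcile the abstract's list of secondary failure outcomes with the body. If the supplement already specifies cumulative analyses, align the article's sentence with it.

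The cost is wording only: the same adjudicated data are used, with no extra participants or data collection.
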